## Abstract

**Background:**

Poor person-centered maternal care (PCMC) contributes to high maternal mortality and morbidity, directly and indirectly, through lack of, delayed, inadequate, unnecessary, or harmful care. While evidence on poor PCMC prevalence, as well as inequities, expanded in the last decade, there is still a significant gap in evidence-based interventions to address PCMC. We describe the protocol for a trial to test the effectiveness of the ***“Caring for Providers to Improve Patient Experience” (CPIPE)*** intervention, which includes five strategies, targeting provider stress and bias as intermediate factors to improve PCMC and address inequities.

**Methods:**

The trial will assess the effect of CPIPE on PCMC, as well as on intermediate and distal outcomes, using a two-arm cluster randomized controlled trial in 40 health facilities in *Migori* and *Homa Bay Counties* in Kenya and *Upper East* and *Northeast Regions* in Ghana. Twenty facilities in each country will be randomized to 10 intervention and 10 control sites. The primary intervention targets are all healthcare workers who provide maternal health services. The intervention impact will be assessed among healthcare workers in the study health facilities and among women who give birth in the study health facilities. The primary outcome is PCMC measured with the PCMC scale, via multiple cross-sectional surveys of mothers who gave birth in the preceding 12 weeks in study facilities at baseline (prior to the intervention), midline (6 months after intervention start), and endline (12 months post-baseline) (*N* = 2000 across both countries at each time point). Additionally, 400 providers in the study facilities across both countries will be followed longitudinally at baseline, midline, and endline, to assess intermediate outcomes. The trial incorporates a mixed-methods design; survey data alongside in-depth interviews (IDIs) with healthcare facility leaders, providers, and mothers to qualitatively explore factors influencing the outcomes. Finally, we will collect process and cost data to assess intervention fidelity and cost-effectiveness.

**Discussion:**

This trial will be the first to rigorously assess an intervention to improve PCMC that addresses both provider stress and bias and will advance the evidence base for interventions to improve PCMC and contribute to equity in maternal and neonatal health.

**Trial registration:**

ClinicalTrials.gov: NCT06085105. Protocol version and date: v2-11-07-23

**Supplementary Information:**

The online version contains supplementary material available at 10.1186/s12889-024-20023-9.

## Background

Maternal mortality and morbidity remain very high in sub-Saharan Africa (SSA), despite progress in the last decade [1]. The estimated maternal mortality ratio for SSA is 546 per 100,000 live births—with Ghana and Kenya at 308 and 510, respectively, compared to about 12 in high-income regions [1]. Further, for every woman who dies, about 20 others suffer from various morbidities [2]. These outcomes occur alongside poor fetal outcomes including stillbirths, prematurity, and early neonatal deaths. High quality care during childbirth is critical for preventing maternal and neonatal mortality, given roughly three-quarters of maternal and fetal deaths occur from complications during labor, delivery, and the first 24 h postpartum [3]. While complications are difficult to predict, they can effectively be managed, and deaths averted when recognized and treated promptly [3, 4]. Thus, skilled care by health professionals who can identify and treat complications and provide basic care and referrals, are essential at every delivery [3].

Until recently, most efforts to improve maternal and child health (MCH) outcomes in SSA focused on increasing the use of MCH services. While countries in SSA, such as Ghana and Kenya, report increasing coverage for facility births, significant gaps in equity and quality of care persist between and within countries [5]. For instance, although about 70% of births in SSA occur in health facilities, wide disparities in facility-based births persist, especially by SES [6]. Further, poor quality care in many health facilities, coupled with the lack of reduction in mortality on par with increased facility deliveries, has called attention to the quality of care [7–9]. Quality of care includes both service provision and experience of care [10]. Most efforts have, however, emphasized service provision—the technical aspects of quality of care; fewer address experience of care—the person-centered dimensions and vehicle by which care is delivered [11].

Person-centered maternity care (PCMC) is a key component of quality of care that captures the interpersonal aspects of care and impacts patient experience. It emphasizes maternal healthcare that is respectful, compassionate, and responsive to individual patient preferences, needs, and values [12]. Key domains of PCMC include dignity and respect, communication and autonomy, and supportive care. PCMC is a critical component of a human rights framework, as everyone has a right to be treated with dignity and respect, including during pregnancy and childbirth [13–16]. However, globally, studies have shown significant gaps in PCMC as evidenced by disrespect and abuse, poor communication, lack of respect for women’s autonomy, and lack of supportive care during prenatal care and childbirth [17–20]. Such poor PCMC contributes to both the low rates of facility-based deliveries and the disparities [21, 22], with the poorest outcomes among the most vulnerable, who are more likely to be mistreated and stigmatized in health facilities [18, 19, 23, 24]. Further, PCMC contributes to improved health outcomes through timeliness, patient engagement, safety, improved psychosocial health, and patient and provider satisfaction [25, 26]. Recent research also shows PCMC domains are associated with improved maternal and neonatal outcomes such as shorter duration of labor, decreased cesarean and instrumental vaginal birth, higher five-minute Apgar scores, early postnatal care, breastfeeding, and lower risk of screening positive for post-partum depression [27–32]. Poor PCMC, therefore, undermines health gains for mothers and babies [33].

Several studies have highlighted the multilevel drivers of poor PCMC, which include inadequate provider knowledge of PCMC, poor provider attitudes, provider stress, burnout, and bias, power asymmetry between patients and providers, lack of accountability mechanisms, institutional and health system factors, and broader social and gender norms that facilitate and normalize disrespect and abuse [34–41]. There is, however, still limited research on interventions to improve PCMC in LMICs, with most interventions focused on individual drivers such as provider knowledge [42, 43]. Further, existing interventions in LMICs do not address the role of provider stress, burnout, and difficult patient-provider interactions in PCMC, nor do they explicitly address the inequities in PCMC [38, 44–46]. To address the gap in evidence-based interventions to improve PCMC, we designed the “Caring for Providers to Improve Patient Experience” (CPIPE) intervention to address drivers of poor PCMC and center the unique needs of vulnerable women in LMICs. The development of the intervention has been previously described in detail [47].

CPIPE is a theory and evidence-based intervention that was designed through an iterative process of formative research and feedback from stakeholders, and informed by the Ecological Perspective [48], Social Cognitive Theory [49], and Trauma Informed System framework [50]. It leverages 5 strategies: provider simulation-enhanced training, peer support, mentorship, embedded champions, and leadership engagement (Fig. 1). The training, which is delivered through short didactic, interactive training, and reflective sessions over 2 days, includes content on PCMC, stress management, dealing with difficult situations, and implicit and explicit bias. This content is integrated into customized highly realistic emergency obstetric and neonatal care (EmONC) simulations and teamwork and communication activities designed in collaboration with PRONTO International to enable providers to apply concepts in the context of an emergency scenario with guided self-reflection through debriefing [51]. The two-day training is followed by monthly refreshers for six months, as well as resources shared on WhatsApp to reinforce training content over 6 months. Peer support groups are cadre-specific groups of the providers that are facilitated monthly by a peer leader to debrief on events at the maternity unit, brainstorm solutions, and engage in stress management activities. Mentorship involves intentional mentor-mentee pairing based on a survey of mentor and mentee needs and preferences to facilitate the transfer of knowledge and skills through one-on-one relationships. Embedded champions are selected by their peers in each facility to lead intervention activities in their facility, including facilitating the monthly refreshers and peer support groups. As part of our leadership engagement, a Community Advisory Board (CAB), with representatives from the county/regional, facility, as well as providers and patients, guides the implementation and serves as a body for high-level advocacy. The 2-day training aims to increase provider knowledge, skills, and self-efficacy to impact attitudes and behaviors towards preventing burnout, mitigating bias, and improving PCMC while the additional strategies create an enabling environment for behavior change.

**Fig. 1 Fig1:**
[figure not shown]
CPIPE Intervention strategies

A pilot study in Kenya showed the CPIPE intervention has high feasibility, acceptability, and preliminary effectiveness on provider stress, burnout, bias, and provider-reported PCMC provision [20, 52]. Thus, the next step is to assess the effectiveness of *CPIPE* on patient-reported measures and to explore *CPIPE’s* mechanisms of action in a rigorously designed and fully powered study. This paper describes the protocol for this next phase of our work.

## Methods

### Aims

Our specific aims, as shown in Fig. 2, are to:

**Fig. 2 Fig2:**
[figure not shown]
CPIPE conceptual framework

#### Assess the effectiveness of the CPIPE intervention on PCMC

We hypothesize that *CPIPE* will improve PCMC for all women, but especially for low SES women. In addition, we will conduct a cost-effectiveness analysis of CPIPE on PCMC.

#### Examine the mechanisms of impact of CPIPE

We hypothesize that CPIPE will improve intermediate outcomes (provider knowledge and self-efficacy, stress, burnout, and bias levels), which will, in turn, impact PCMC. We will assess the effect of the intervention on these intermediate outcomes and examine if changes in these outcomes account for the effect of *CPIPE* on PCMC. We will also assess implementation outcomes, including fidelity and quality of implementation, that may contribute to differential effects.

#### Assess the impact of the CPIPE intervention on distal outcomes

This is an exploratory aim in which we will examine if the intervention impacts more distal outcomes in our conceptual framework, including timely postnatal care, breastfeeding initiation and exclusivity, postpartum mental well-being, neonatal complications, and maternal and neonatal mortality, and if changes in PCMC account for these effects.

### Study design and setting

We plan to test the effectiveness of the *CPIPE intervention* on PCMC and intermediate and distal outcomes using a two-arm cluster randomized controlled trial (RCT) in 40 high volume health facilities in Migori and Homa Bay Counties in western Kenya and in the Upper East and Northeast Regions of northern Ghana. The counties and regions in each country were selected for having among the worst maternal and neonatal health outcomes, having similar characteristics, and based on our existing institutional relationships. Migori and Homabay are neighboring, and similar counties located along Lake Victoria in in western Kenya that have comparable maternal and neonatal mortality burden. They have 8 sub-counties, each with a sub-county hospital and one county referral hospital. There are about 155 and 263 health facilities in Migori and Homa Bay, respectively, including county and sub-county hospitals, health centers, faith-based, and private health facilities [53]. The Upper East and North East Regions are also neighboring regions located in the north-eastern corner of Ghana, both sharing borders with Togo to the east that also have similar characteristics and maternal and neonatal mortality burden. The Upper East Region shares boundaries with Burkina Faso to the north and Northeast Region to the south. The Upper East region is divided into 15 districts, with 11 district hospital, 67 health centers, 419 CHPS compounds and one regional hospital that serves as a referral center for the district hospitals [54, 55]. Northeast is divided into six districts, with five district hospitals, 21 health centers, and 154 CHPS compounds [56].

### Randomization

Randomizing individual providers is not ideal because of a high potential for contamination within facilities and goal of changing facility culture. A cluster RCT design allows us to address threats to internal validity and account for natural clustering of providers within facilities [57]. Forty facilities will be randomized to intervention (*N* = 20) and control (*N* = 20), with arms stratified by country(10 intervention and 10 control facilities in each country). To reduce the risk of contamination due to interaction of providers within the same sub-counties and districts, randomization will be at the sub-county/district level such that control and intervention facilities are not in the same sub-county/district. The facility randomization will be done by a statistician not directly involved in the study. The intervention group will receive all strategies of the *CPIPE* intervention strategies over a period of 6 months after the baseline data collection. At the end of the 6-month implementation, we will collect midline data. Facilities will then be encouraged to continue with the intervention activities without involvement of the study for an additional 6 months, with final data collection at 12 months (endline). The control group will not receive the CPIPE intervention during the 12-month data collection period but will maintain their usual facility level activities. We plan to implement the intervention in the control sites after the endline data collection (assuming preliminary effectiveness). The protocol complies with the standard protocol items for cluster randomized trials. The study design, outcomes, and participant flow are summarized in Figs. 2 and 3.

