### Analysis plan

#### Data quality assurance, initial analyses, and missing data

We will use Redcap to perform real-time checks for data quality assurance [69, 70]. We will use frequency tables and measures of central tendency and variability for continuous variables to characterize the sample overall and by randomization group. If the two groups differ significantly at baseline on one or more covariates, we will use methods based on the Rubin causal model (e.g., propensity scores, double-robust estimation) to obtain the desired effect estimates under the counterfactual assumption of balanced groups [71, 72]. We will address incomplete data with direct maximum likelihood (ML) and multiple imputation (MI) [73] because they make the relatively mild assumption that incomplete data arise from a conditionally missing-at-random (MAR) mechanism [74]. Auxiliary variables will be included to help meet the MAR assumption [75]. The proposed analyses will be conducted using STATA. All program code and results will be documented extensively and archived to enable future review, transparency, and results reproducibility.

##### Aim 1

We hypothesize that mothers in the *CPIPE* intervention group will have higher mean PCMC scores than mothers in the control group at 6 months (H1a) and 12 months (H1b) after baseline. To test hypotheses H1a-H1b, in primary analyses we will fit two-level linear mixed models (LMM) to the PCMC score. Each of these two models will include a fixed effect for the study arm with random intercepts for facility ID to account for the clustering of women within health facilities. Because we will compare *CPIPE* to control at 6 months and then repeat the same comparison at 12 months, alpha (α) will be set at 0.05/2 = 0.025 for each of these two planned comparisons. In secondary analyses for Aim 1, we will extend the LMMs for PCMC to include effects for age and SES and their interactions with the intervention group indicator to explore whether the *CPIPE* intervention differentially benefits younger and lower SES women. Sex as a Biological Variable is not applicable: all participants will be biological females.

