##### Aim 1 Power Analysis:

We used the NCSS PASS [76] module for a two-level multilevel model with a continuous outcome and randomization at the cluster (i.e., health facility) level to compute the minimum detectable effect size estimates for hypotheses H1a-H1b. We assumed power of 0.80, α = 0.025 per comparison, and *N* = 2000 women from 40 facilities. We further assumed ICC = 0.16 based on our previous data [20, 77]. The minimum detectable standardized mean difference was *d* = 0.41, which is between small and medium effect size, suggesting the proposed primary analyses have sufficient power to detect small to medium effects [78].

##### Aim 2

We anticipate that the intervention will positively impact the intermediate outcomes in our conceptual model (Fig. 1), leading to an improvement in PCMC. We thus hypothesize that, following *CPIPE* exposure, intervention providers will have, higher mean scores on provider knowledge (H2a); self-efficacy (H2b); enabling environment (H2c); behavior (H2d), and lower mean scores on work-related psychological effects (stress, burnout, and bias) (H2e) relative to control providers. To test these hypotheses, we will fit three-level LMMs to each intermediate outcome, with fixed effects for study arm, time, and their interaction, random intercepts for facility ID to account for clustering of providers within health facilities, and random intercepts, random slopes, and their covariance for person ID to account for clustering of repeated measurements within providers. We will perform time-averaged comparisons of repeatedly measured post-baseline observations of the key intermediate outcomes across study arms to examine *CPIPE* intervention effects.

In secondary exploratory analyses, we will investigate whether the intermediate outcomes measured for providers at 6 months mediate the relationship between *CPIPE* intervention assignment and PCMC at 12 months. These analyses will be conducted using principles of structural equation modeling (SEM) and causal mediation methods [1]. We will explore whether *sex as a biological variable* differentially affects intervention effects on the provider-level primary analyses by adding a sex main effect and a sex-by-*CPIPE* assignment interaction term to the LMM models. Sex as a biological variable is not applicable to the mediation analyses due to the outcome applying to women only.

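### Allocation is described at sub-county/district level, but the outcome models and the stated detectable effect of d = 0.41 treat the facility as the randomised unit

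*Protocol article*

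**What the plan says.** The Randomization section of the protocol article gives two descriptions of the allocated unit. It opens with "Forty facilities will be randomized to intervention", balanced as "10 intervention and 10 control facilities in each country". It then states that "randomization will be at the sub-county/district level such that control and intervention facilities are not in the same sub-county/district". The reason given is to limit contamination through contact between providers in the same area.

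The Aim 1 analysis tests PCMC at 6 and 12 months with two-level linear mixed models: "Each of these two models will include a fixed effect for the study arm with random intercepts for facility ID". No sub-county or district term is named. The Aim 1 power analysis assumes "randomization at the cluster (i.e., health facility) level", with 2000 women in 40 facilities, one ICC of 0.16, power 0.80 and alpha 0.025 per comparison, and arrives at d = 0.41.

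The Aim 2 models have random effects for facility and provider, and the Aim 3 models for facility. Neither includes the sub-county/district.

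On geography, Study design and setting says of the two Kenyan counties: "They have 8 sub-counties, each with a sub-county hospital and one county referral hospital". For Ghana it gives 15 districts in Upper East and six in Northeast.

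**The concern.** If sub-counties and districts are allocated, all study facilities in one of them always share an arm. Such facilities are independent replicates of the arm contrast only if nothing beyond the facility makes women in the same area alike. A model that stops at the facility counts 40 independent units whatever the number allocated. Where areas differ, its standard error for the arm effect tends to be too small, and a power calculation based on 40 units is too favourable. This affects the confirmatory test of the primary outcome at both time points, and the Aim 2 and Aim 3 tests share the structure.

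**Working it through.** **1. Can every facility be its own randomised unit?** Not in Kenya. The sub-county sentence can mean 8 in each county (16) or 8 in all, for 20 facilities. Ghana has 15 + 6 = 21 districts for 20 facilities, so one each is possible there. The most units that can be randomised are 16 + 20 = 36, or 8 + 20 = 28.

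**2. Reproducing the stated figure.** Women per facility: 2000/40 = 50. Design effect: 1 + 49 × 0.16 = 8.84. Variance of the arm difference: 2 × 8.84/1000 = 0.01768, so SE = 0.133. Two-sided, d = (2.241 + 0.842) × 0.133 = 0.410. The article's 0.41 is therefore right for 40 independently randomised facilities.

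**3. Adding the district level.** The article does not split the ICC. Let a share s of the 0.16 lie between districts (assumption: 25% to 75%). Let n_j be the number of facilities in district j of one arm and Q = Σn_j², with 10 facilities per arm and country spread as evenly as possible.

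True variance = 2 × [s × 0.16 × Q/400 + (1 − s) × 0.16/20 + 0.84/1000].

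- 36 units: per arm, Kenya 2, 2 and six single facilities (sum of squares 14), Ghana ten single (10). Q = 24.
- 28 units: per arm, Kenya 3, 3, 2, 2 (26), Ghana ten single (10). Q = 36.

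The detectable effect is 3.083 × the square root of this variance, on the same normal scale as the 0.41. Power at 0.41 is Φ(0.41/SE − 2.241).

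**4. Type I error of the facility-only test.** A facility mean has variance 0.16 + 0.84/50 = 0.1768. A facility-level test, which stands in for the balanced facility-only mixed model, estimates on average 2 × [0.1768 − s × 0.16 × (Q − 20)/380]/20. If R is the square root of true over estimated variance, the actual error is about P(|t38| > 2.334/R).

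| Units | s | True variance | Detectable d | Power at 0.41 | Estimated variance | R | Type I error |
|---|---|---|---|---|---|---|---|
| any | 0 | 0.01768 | 0.410 | 80% | 0.01768 | 1.000 | 0.025 |
| 36 | 25% | 0.01848 | 0.419 | 78% | 0.01764 | 1.024 | 0.028 |
| 36 | 75% | 0.02008 | 0.437 | 74% | 0.01755 | 1.070 | 0.035 |
| 28 | 25% | 0.02088 | 0.445 | 72% | 0.01751 | 1.092 | 0.039 |
| 28 | 75% | 0.02728 | 0.509 | 60% | 0.01717 | 1.260 | 0.072 |

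Simulation of facility means agrees with the last column to within about 0.001 to 0.002.

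**The case against.** The strongest reply is that nothing in the article shows variance between districts. Contact between providers is given as a reason to fear contamination, not as a variance component. If that variance is zero, 0.41 and 0.025 stand. This is correct, and the conclusion must stay conditional. Still, zero is hard to assume where the plan itself treats facilities in one area as linked.

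A second reply is that a bias runs the other way. Allocation is balanced by country, but the stated Aim 1 model names no country term. A difference in mean PCMC between Kenya and Ghana would then enter the estimated facility variance without affecting the arm contrast, which makes the test conservative. As an illustration, let a share c of the 0.16 lie between countries and split the rest as above. This adds c × 0.16 × 20/19 to the estimated facility variance.

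- 36 units, c = 10%: R is √(0.01680/0.01773) = 0.974 at s = 25% and √(0.01824/0.01765) = 1.017 at s = 75%. The error is about 0.021 to 0.027.
- 28 units, c = 20%: R is √(0.01704/0.01771) = 0.981 and √(0.02216/0.01744) = 1.127. The error is about 0.022 to 0.045.

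This stands. The net direction of the type I error is not established in the mildest case, although two misspecifications that may cancel are no basis for a test. The offset does nothing to restore the number of randomised units.

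A third reply is that the choice between normal and t critical values is a separate matter, usually left to the SAP. That is so, and it is not counted here: the detectable effects use the article's normal scale, and the error rates use a t reference that gives 0.025 when s = 0.

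A reader might also infer that only about 20 units are randomised, which gives a much larger loss. The article does not say so; 21 Ghanaian districts are enough for one facility each.

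**Conclusion.** The point holds in conditional form. The article describes allocation by sub-county/district but analyses and powers the trial as if 40 facilities were allocated independently. Its own geography makes that impossible in Kenya under area-level allocation. The 0.41 is not an arithmetic error; it answers a different design.

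If a quarter to three quarters of the 0.16 lies between districts (assumption), the detectable effect is about 0.42-0.44 with 36 units and 0.445-0.51 with 28. The type I error is about 0.028-0.035 and 0.039-0.072, before any country offset. With fewer units the effect is larger. The article gives neither the number of units nor a district-level ICC, so no single corrected figure can be quoted.

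Two stronger readings are tempting. One is that the type I error certainly exceeds 0.025, which would need a positive district variance and no sizeable country difference. The other is that the sentence about forty facilities is the mistaken one. The article does not settle which of its two descriptions was intended.

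**What to change.** State one unit of randomisation and the number of units in each country, with the study facilities in each.

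- **If the unit is the sub-county/district:** account for that level in the Aim 1, 2 and 3 models. Either add a sub-county/district random intercept with facility nested within it, or analyse at sub-county/district level. Base small-sample degrees of freedom on the randomised units. With 36 units only four would hold two facilities, so the two variances would be hard to separate and the district-level analysis may be more stable. Restate the Aim 1-3 detectable effects for the actual number of units over a range of district-level ICCs.
- **If the unit is the facility:** correct the Randomization section instead. The models and the 0.41 can then stay on this point.

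The cost is wording, a rerun of the power calculation, a somewhat less favourable detectable effect and a little more analysis work. No extra data are needed.
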